### Study procedures WBRT

On a gadolinium contrast-enhanced (single – triple dose Gd is allowed) MRI (1.0 T–3 T) with a maximal slice thickness of 1.5 mm, the definitive number of BM and the definitive maximum lesion diameter in any direction of the largest BM are determined. Patients randomised for WBRT will be treated with five fractions of 4 Gy up to a total dose of 20 Gy delivered in five consecutive working days. Dose prescription is according to ICRU 50 criteria. [4] The brain is contoured as a clinical target volume (CTV) until the foramen magnum. The CTV is equal to the PTV. To determine the size of the GTVs of the metastases, all BMs and lenses are contoured. Patients are positioned with a mask. The use of a planning CT is mandatory with slice thickness of ≤3 mm. The use of a contrast medium is not obliged. The planning-MRI is co-registered for contouring of the BM. The daily prescription dose will be 4 Gy prescribed at the ICRU reference point, and the 95% isodose must encompass 99% of the planning target volume (PTV); the maximum dose to the PTV should not exceed 107% of the prescribed dose. Generally, two opposed lateral fields are used with shielding of lenses and the pharyngeal space. All techniques that result in the dose requirements being met are allowed.

### Study procedures of SRS

Only single fraction treatments are allowed within this protocol. For any given patient, all brain metastases will be treated with the same dose, which will be determined by the PTV of the largest BM or brainstem location in the range of 15–24 Gy. (Table 1) The dose gradient outside the PTV will be as steep as possible to spare healthy brain tissue. Within the PTV, there will be considerable dose inhomogeneity, with a maximum allowed dose within the PTV of 140% of the prescribed dose. The GTV is defined by contouring the outer contrast-enhancing border of the BM on T1 gadolinium-weighted MRI images. BM are named GTVp1, GTVp2, GTVp3, from the cranial to the caudal side. Organs at risk (brainstem, optic nerves, chiasma, pituary gland, cochleae, and lenses) are contoured according to Scoccianti et al. [5]. The PTV is defined by a 0–2 mm isotropic expansion of the GTV, according to institutional standards for SRS. If a BM is within or adjacent to the brainstem, the PTV margin will be 0 mm. If in an institution, a smaller GTV to PTV margin is used when lesions are treated using multiple isocentres, then this technique is to be considered to reduce the V12_Gy_ of the largest BM if it would otherwise be more than 10 cm^3^.

**Table 1 Tab1:** Risk adapted SRS dose prescription volume and location based

PTV of the largest brain metastasis	Doses in each PTV	BM in brainstem (GTV = PTV)
<1 cm^3^	1 × 24 Gy	1× 16Gy
1–10 cm^3^	1 × 21 Gy	1 x 16Gy
10–20 cm^3^	1 × 18 Gy	1 x 16Gy
20–65 cm^3^	1 × 15 Gy	No SRS

All BMs are dosed equally in the same patient. If the V12 Gy exceeds 10 cm^3^ of the healthy brain tissue nearby the largest brain metastasis, it is allowed to lower the fraction dose to a single dose of 21, 18 or 15 Gy

Patients will be immobilised in a supine position within a thermoplastic mask or stereotactic noninvasive frame, with or without bite block and/or other fixation, according to institutional standards for SRS. The accuracy of the stereotactic fixation system should be good enough to justify the CTV to PTV margin used. This means the intrafraction motion should at least be within the CTV-PTV margin used. If a margin of 0 mm is used, the maximum intrafraction motion should be <0.5 mm, with the SD being less than 0.25 mm. A planning CT scan with ≤2 mm thick contiguous slices (preferable CT slice thickness = 1 mm) will be fused to a contrast-enhanced stereotactic MRI scan. The interval between the planning-MRI and actual SRS treatment is a maximum of 3 weeks. Single or multiple isocentres are allowed for delivering SRS according to the preference of treatment center. Tissue density inhomogeneity correction will be used. Positional verification and correction prior to (and/or during) radiation should be executed according to the institutional protocol for stereotactic radiotherapy and should be in accordance with the CTV-PTV margin used. All techniques that result in the dose requirements being met are allowed. Participating institutes will have to define their radiation delivery treatment prior to the initiation of the study. Techniques that have a shorter treatment time duration are preferred as this is more comfortable for the patient and might prevent an increase in the intrafraction displacement over the treatment time. All vendors are allowed to deliver SRS, such as a linear accelerator, Gamma Knife and CyberKnife.

### Number of patients and recruitment

Questionnaires measuring QOL with the EQ5D EUROQOL questionnaire are collected from patients with multiple BM treated with WBRT or SRS at baseline and at 3 months after treatment. For this phase III trial, sample size calculation is based on the clinically relevant difference of 0.10 points of the EQ5D-5 L index value (range 0–1) at 3 months after treatment with regard to baseline, with a standard deviation of 0.25 points. For every patient this difference in EQ5D-5 L QOL score is calculated (score at 3 months minus score at baseline). The average score of all patients in the SRS group is calculated and this average score is compared to the calculated average score of all patients in the WBRT group. This is accordingly the method described by Pickard. [6] Sample size calculation is performed for a comparison of means with two-sided alpha 0.05 and power of 0.80. This leads to a sample size per group of 100 patients. To account for drop out, the sample size for this study will be increased by 15% to 230 patients (115 per group). After 86 patients treated, an interim analysis is performed to monitor the safety of the trial regarding the experimental SRS arm.

Patient accrual was started on 1^st^ July, 2016. Up to 14^th^ April, 2017, nine patients were randomised. With expected participation of 12 centres, it is estimated that patient’s accrual can be completed within 2 years with an expected accrual of 10–15 patients each year per centre.

For this phase III study, a comparison of the above described difference in EQ5D score between SRS and WBRT group will be performed using an independent samples Student’s t-test with two-sided significance level alpha set at 0.05. A clinical significant difference in EQ5D is determined at 0.10 points in the index score. [4] For the total patient cohort, a multivariate analysis is performed to identify prognostic factors for a difference in EQ5D score at 3 months with regard to baseline. Differences in secondary endpoints that repeat in time are analysed with Kaplan Meyer curves including log-rank test or ANOVA test. Time-to-event data (e.g. overall survival) will be compared using Kaplan–Meier curves and log-rank test. Means will be compared using independent samples Student’s t-tests. Frequencies (e.g. WHO-PFS) will be compared using Chi-square test.

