### Objectives and endpoints

The primary objective is to determine whether QOL is better preserved after SRS than after WBRT in patients with 4–10 BM. The primary endpoint is difference in QOL (EQ5D EUROQOL score) at 3 months after radiotherapy with regard to baseline. The secondary objective is to determine whether SRS provides better survival and less toxicity than WBRT. [1, 2] Secondary endpoints are difference in QOL (EQ5D EUROQOL questionnaire) at 6, 9 and 12 months after radiotherapy with regard to baseline, survival at 3, 6, 9 and 12 months after radiotherapy, Karnofsky ≥ 70, WHO performance status, steroid use (mg), toxicity according CTCAE V4.0 including hair loss, fatigue, neurocognition and brain salvage during follow-up, type of salvage, time to salvage after randomisation and Barthel index. Facultative secondary endpoints are neurocognition with the Hopkins verbal learning test, quality of life EORTC QLQ-C30, quality of life EORTC BN20 brain module and fatigue scale EORTC QLQ-FA13.

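### The primary t-test on the EQ5D-5L change score is valid but does not adjust for baseline; ANCOVA on the same patients would usually be more precise, by an amount the article does not allow one to fix

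*Protocol article*

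**What the plan says.** Under Objectives and endpoints the article states: "The primary endpoint is difference in QOL (EQ5D EUROQOL score) at 3 months after radiotherapy with regard to baseline". Number of patients and recruitment makes this a per-patient change: "For every patient this difference in EQ5D-5 L QOL score is calculated (score at 3 months minus score at baseline"). The changes are averaged within each arm and the two averages are compared.

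The same section sets out the primary analysis: "a comparison of the above described difference in EQ5D score between SRS and WBRT group will be performed using an independent samples" procedure, namely the one due to Student. The level attached to it is stated as "t-test with two-sided significance level alpha set at 0.05". No covariate is named.

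The sample size follows the same comparison. Its target is a "clinically relevant difference of 0.10 points of the EQ5D-5 L index value (range 0–1) at 3 months after treatment with regard to baseline". The spread assumed for it appears in the words "with a standard deviation of 0.25 points". On error rates the section says: "Sample size calculation is performed for a comparison of means with two-sided alpha 0.05 and power of 0.80". The result that it reports is: "This leads to a sample size per group of 100 patients".

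The section also mentions a multivariate analysis, but that is run on the pooled cohort to look for prognostic factors. It is not the comparison of the arms, so it does not supply baseline adjustment for the primary result.

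**The concern.** A change score uses the baseline value in one particular way: it subtracts all of it, which amounts to a regression slope of exactly 1. The slope that minimises the residual variance is rho × k, where rho is the correlation between the baseline and 3-month scores and k is the 3-month SD divided by the baseline SD. Unless rho × k happens to equal 1, the change score carries variance that estimating the slope would remove.

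The second consequence concerns chance imbalance. If one arm starts with a higher mean EQ-5D by luck, its mean change is expected to be lower by (1 - rho × k) times the imbalance when rho × k is below 1. The t-test leaves that shift in the estimate; ANCOVA takes it out.

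What is at stake is precision in a trial sized at 80% power with almost no slack. Every patient who contributes a change score has a baseline score by definition, so adjustment needs no new data and loses no one.

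**Working it through.** **Inputs from the article (Number of patients and recruitment):** difference 0.10; SD 0.25, read as the SD of the change score; two-sided alpha 0.05; power 0.80; 100 evaluable per group.

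**Inputs not in the article:** rho, and the separate SDs at the two visits. Both are assumptions here: rho 0.3 to 0.7, and k = 0.8, 1 and 1.25.

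**Step 1: reproduce the stated figure.** n per group = 2 × (1.960 + 0.8416)² × 0.25² / 0.10² = 2 × 7.849 × 6.25 = 98.1, so 99. The t-distribution solution is 99.1, so 100. The article's 100 reproduces. Power at 100 per group is 80.7% by the normal formula and 80.4% by the t-test.

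**Step 2: fraction of variance removed by ANCOVA.** In units of the baseline variance:
- change score: 1 + k² - 2 × rho × k
- ANCOVA residual: k² × (1 - rho²)
- difference between the two: (1 - rho × k)²

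So the fraction removed is r = (1 - rho × k)² / (1 + k² - 2 × rho × k). With equal SDs (k = 1) this reduces to (1 - rho)/2.

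**Step 3: power at 100 evaluable per group.** The unadjusted standard error is 0.25 × √(2/100) = 0.03536, and 0.10/0.03536 = 2.828. With fraction r removed, power = Φ(2.828/√(1 - r) - 1.96). With r = 0 this is Φ(0.868) = 80.7%.

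| k | rho | Variance removed | Effective SD | Power |
|---|---|---|---|---|
| 1 | 0.3 | 35% | 0.202 | 93.9% |
| 1 | 0.5 | 25% | 0.217 | 90.4% |
| 1 | 0.7 | 15% | 0.230 | 86.6% |
| 1.25 | 0.3 | 22% | 0.221 | 89.1% |
| 1.25 | 0.5 | 11% | 0.236 | 84.9% |
| 1.25 | 0.7 | 2% | 0.248 | 81.5% |
| 0.8 | 0.3 | 50% | 0.177 | 97.9% |
| 0.8 | 0.5 | 43% | 0.189 | 96.3% |
| 0.8 | 0.7 | 37% | 0.198 | 94.6% |

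Example, k = 1.25 and rho = 0.7: (1 - 0.875)² / (1 + 1.5625 - 1.75) = 0.0156/0.8125 = 0.019.

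With equal SDs, the number per group for 80% power falls from 99 to 64, 74 or 84 for rho 0.3, 0.5 or 0.7 (normal formula).

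**Step 4: simulation check.** With equal SDs, 100 per group and 4,000 runs, the variance removed was 34.7%, 25.6% and 14.3% for rho 0.3, 0.5 and 0.7. ANCOVA power was 93%, 90% and 86%, against 80-81% for the t-test.

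**Step 5: where the gain vanishes.** With rho = 0.8 and k = 1.25, rho × k = 1 and r = 0. The change score is then already optimal.

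**Step 6: size of the conditional shift.** Take equal SDs and rho = 0.5. The SD at each visit is 0.25/√(2 × 0.5) = 0.25, so the standard error of the baseline difference is 0.25 × √(2/100) = 0.035. An imbalance of one standard error shifts the change-score estimate by 0.5 × 0.035 = 0.018, which is 18% of the 0.10 target. An imbalance of two standard errors shifts it by 0.035.

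**Sensitivity to reading the 0.25.** If it were the SD of a single score, then with equal SDs the number per group for 80% power would be 138, 99 and 59 for the t-test, against 90, 74 and 51 for ANCOVA (rho 0.3, 0.5, 0.7). The direction is the same.

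**The case against.** The strongest reply is that nothing here is wrong. The endpoint is a change, the test compares mean changes, and the sample size is for that comparison and reproduces. Under randomisation the t-test holds its alpha and is unbiased. All of that stands, and it makes this a missed gain in precision rather than an error.

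The reply also limits how far the point can be pushed. A reader might infer any of the following, and the article supports none of them:

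- *That 15-35% of the variance is lost as a matter of fact.* That range needs rho between 0.3 and 0.7 and equal SDs at both visits, and the article gives neither. Entry requires a Karnofsky score of at least 70 (Study population). This may narrow the baseline spread and let scores diverge later; k would then exceed 1 and the saving could be as low as 2%.
- *That any correlation below 1 leaves noise to remove.* This holds with equal SDs. In general the condition is rho × k different from 1.
- *That the planned estimate is biased.* It is not, over randomisations. The shift in step 6 is conditional on an imbalance that has occurred by chance.
- *That adjustment makes up for lost patients.* ANCOVA as proposed uses the same patients with both scores. It does not address 3-month scores missing through death or dropout.

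It might also be said that a separate analysis plan could add the covariate. The article does not leave the choice open, however: it names the primary test, and an adjusted primary analysis would depart from what it states.

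**Conclusion.** The point stands as lost precision. The article fixes an unadjusted t-test on change when a baseline-adjusted analysis of the same patients targets the same difference and in large samples is never less efficient. The cost is one degree of freedom, negligible with about 200 patients.

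The direction is firm; the size is not. With equal SDs and rho from 0.3 to 0.7, power at 100 evaluable per group would be about 87-94% instead of about 80%. Over SD ratios from 0.8 to 1.25 the variance saved runs from about 50% down to about 2%, and it is nil when rho × k equals 1. Alpha, the stated power and the planned 230 patients are not called into question by this point.

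**What to change.** Before any comparison of the arms on EQ-5D, restate the primary analysis as follows: a linear model of the 3-month EQ5D-5L index on treatment arm, with the baseline index as covariate and any factors used to stratify randomisation, tested at two-sided 0.05 and reported with a 95% confidence interval. Modelling the change instead of the 3-month score, with baseline still in the model, gives the identical treatment estimate, so the endpoint can stay as defined. Keep the t-test on change as a supporting analysis.

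The cost is about a sentence of analysis wording and one degree of freedom, with no new data. The sample size need not change: 100 per group was derived for the unadjusted test, so in large samples it is sufficient or better for the adjusted one under the same assumptions. The handling of missing 3-month scores has to be settled separately.

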## Discussion

A typical SRS treatment requires a high-resolution contrast-enhanced planning-MRI, frameless mask, a planning-CT, a treatment plan and quality assurance. Generally, all preparations will take a maximum of 2 weeks. Duration of SRS delivery depends on the number of isocentres, arcs and dose rate, but usually in the range of several minutes up to 45 min. With WBRT, all other preparation steps are required, but treatment planning and quality assurance are less complex. WBRT treatment is delivered in five fractions compared to a single treatment fraction with SRS. Questionnaires will be assessed at baseline, 3 months after treatment and every 3 months thereafter until 1 year after treatment. Questionnaires can be assessed by telephone, or during scheduled outpatient clinic visits. Not all hospitals have the logistic capacity to perform neurocognitive tests and extensive QOL assessment; hence, neurocognition (Hopkins Verbal Learning Test) and more extensive QOL (EORTC QLQ-C30, EORTC BN20, and EORTC QLQ-FA13) will be facultative endpoints and will only be performed at baseline and at 3 months after radiotherapy at the outpatient clinic in centres willing to participate. Although these secondary endpoints are facultative, these endpoints will also provide valuable information, and participating centres are recommended to monitor them.

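### The method set for repeated secondary endpoints (log-rank or ANOVA) does not give a suitable analysis for serial scores such as EQ5D at 6, 9 and 12 months

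*Protocol article*

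**What the plan says.** The statistical paragraphs of the protocol article (Number of patients and recruitment) contain four method sentences that bear on secondary endpoints:

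- Repeated measures: "Differences in secondary endpoints that repeat in time are analysed with Kaplan Meyer curves including log-rank test or ANOVA test".
- Events: "Time-to-event data (e.g. overall survival) will be compared using Kaplan–Meier curves and log-rank test".
- Means: "Means will be compared using independent samples Student’s t-tests".
- Frequencies: "Frequencies (e.g. WHO-PFS) will be compared using Chi-square test".

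The endpoints come from Objectives and endpoints: "Secondary endpoints are difference in QOL (EQ5D EUROQOL questionnaire) at 6, 9 and 12 months after radiotherapy with regard to baseline", followed by "survival at 3, 6, 9 and 12 months after radiotherapy", performance status, steroid dose, toxicity, salvage and Barthel index. The Abstract places these other endpoints at 3, 6, 9 and 12 months. The Discussion gives the schedule: "Questionnaires will be assessed at baseline, 3 months after treatment and every 3 months thereafter until 1 year after treatment".

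Time-to-event data have their own sentence, so the sentence on repeated endpoints must at least cover the serial measures.

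**The concern.** For a serial score, the sentence offers two unlike methods.

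- **Log-rank** compares times to an event. The article names no threshold or deterioration that would turn an EQ5D index, Barthel index or steroid dose into an event.
- **ANOVA** is not specified. Applied to all visit records as if independent, it ignores the correlation between visits of one patient and makes the standard error too small. In classical repeated-measures form it handles the correlation, but drops every patient with a missed visit. Survival at the same visits is itself an endpoint, so losses through death are expected.

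The sentence on means adds a third possible route for EQ5D at 6 to 12 months. WHO status repeats in time, yet is also the example given for the chi-square test. What is at stake is whether the quality-of-life results after 3 months can be trusted and are protected from a choice of method made after seeing the data.

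**Working it through.** **The plan's own figure.** Inputs from Number of patients and recruitment: difference 0.10, SD 0.25, two-sided alpha 0.05, power 0.80. Per group, n = 2 × (1.960 + 0.842)² × 0.25² / 0.10² = 98.1, so 99. With the t distribution, power is 0.7997 at 99 and 0.8036 at 100. The stated 100 is reproduced. No figure is attached to the repeated endpoints.

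**Reading A: ordinary ANOVA on pooled visits.** With m visits per patient and within-patient correlation ρ, the variance of an arm mean is inflated by DE = 1 + (m − 1)ρ. The true size of a nominal 5% test is 2 × [1 − Φ(1.96/√DE)]. The documents give no ρ, so 0.3 to 0.7 is assumed. For EQ5D, m = 3, because the 3-month visit is the primary endpoint with its own t-test.

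| ρ | DE (m = 3) | 1.96/√DE | True alpha |
|---|---|---|---|
| 0.3 | 1.6 | 1.550 | 0.121 |
| 0.5 | 2.0 | 1.386 | 0.166 |
| 0.7 | 2.4 | 1.265 | 0.206 |

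For a score with four secondary visits and complete follow-up, DE is 1.9, 2.5 and 3.1, and alpha is 0.155, 0.215 and 0.266.

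Attrition lowers these figures, because fewer patients contribute several visits. Replace m by Σm²/Σm over patients. With exponential survival and an assumed median of 6 to 10 months, the proportions alive at 6, 9 and 12 months are 0.50, 0.35 and 0.25 (median 6) up to 0.66, 0.54 and 0.44 (median 10). Σm²/Σm is then 2.55 to 2.72 in place of 3, and alpha is about 0.11, 0.14 to 0.15, and 0.17 to 0.19.

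**Reading B: classical repeated-measures ANOVA on completers.** In a null simulation (115 per arm, four visits, SD 0.25, equal correlation between visits, 3,000 runs per setting), the between-arm test rejected in 0.046 to 0.053 of trials when loss was unrelated to the score. Correlation is therefore handled. The cost is patients. For a contrast at one visit, power = Φ(0.10 / [0.25 × √(2/n)] − 1.96):

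| Assumed completion | n per arm (of 115) | 0.10 / [0.25 × √(2/n)] | Power |
|---|---|---|---|
| 70% | 80 | 2.530 | 0.72 |
| 50% | 58 | 2.154 | 0.58 |
| 30% | 34 | 1.649 | 0.38 |

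With all 115 per arm the same formula gives 0.86. These are single-visit contrasts. The arm effect averaged over three visits has SD 0.25 × √[(1 + 2ρ)/3], so its power is higher: at ρ = 0.5 about 0.87, 0.75 and 0.52.

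Under health-related death (same score distribution in both arms, ρ = 0.5, 2,000 runs), assumed completion of 40% versus 25% gave a spurious difference of about 0.04 against the arm with better completion, and rejection in about 19% of null trials. With 30% in both arms the difference was about zero and rejection about 5%.

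**Reading C: log-rank on the score.** There is nothing to compute, because no event is defined.

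**The case against.** The case on the other side has real force.

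- A reader might infer that neither method can be valid for repeated endpoints. The article does not support that. Its wording allows repeated-measures ANOVA, which deals with within-patient correlation, and log-rank suits defined events that the trial has, such as time to salvage.
- The choice between the two methods may be meant by endpoint type: log-rank for events, ANOVA for scores. The text does not settle this. Even so, the ANOVA for scores remains open.
- No sentence says that visits will be pooled. EQ5D is defined as a separate change at each visit. One t-test per visit uses one value per patient and has no such inflation. The error rates above therefore belong to one possible reading, and error rates of about 16%, 21% and 27% need four pooled visits with complete follow-up.
- A reader might infer that the 6 to 12 month conclusions must be wrong. That does not follow: with equal completion the completer analysis held its error rate.
- A mixed model does not solve death either.
- The chi-square test is valid for WHO frequencies. An ordered analysis would only gain efficiency.
- A condensed article may leave details to the full protocol or analysis plan. That excuses missing detail. It does not excuse a sentence that names a method which cannot be applied to a serial score without a defined event, or an ANOVA that is unsuitable in its ordinary form and wasteful in its classical repeated-measures form.

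These points narrow the finding but do not rescue the sentence.

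**Conclusion.** The point holds in limited form, and the sentence should be changed. As written, it assigns serial scores to log-rank without an event or to an ANOVA of unstated type. If the ANOVA pools visits, the true alpha for the secondary EQ5D visits is about 0.12 to 0.21, or about 0.11 to 0.19 with attrition. If it is the classical repeated-measures form, alpha is sound when loss is unrelated to the score, but patients with any missed visit are lost, and bias arises if health-related death differs by arm. Correlation, survival and completion are all assumptions, because the documents give none.

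The reach is confined to secondary endpoints. The primary t-test at 3 months and the sample size stand. The facultative questionnaires and the Hopkins test have only one visit after baseline and are not affected.

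**What to change.** Replace the sentence with two rules.

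1. Continuous scores measured repeatedly are analysed with a mixed model for repeated measures with baseline score, arm, visit and arm-by-visit, unstructured covariance and all available visits, and the contrast at each visit is reported. The results are interpreted alongside survival, because the model does not by itself handle death.
2. Kaplan–Meier curves and the log-rank test are kept for explicitly defined events, such as overall survival and time to salvage.

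An ordered analysis of WHO status is optional, as a gain in efficiency and not the correction of an error.

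The cost is a change of wording and slightly more modelling in standard software. No new data are needed. The model recovers patients at the earlier visits who later die or miss a visit; it cannot restore numbers at 12 months.

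### Naming the unequal-variance (Welch) t-test instead of Student's would protect the primary test's 5% level if the scored arms differ in both size and spread, at almost no cost

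*Protocol article*

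**What the plan says.** All of this is in the protocol article, under Number of patients and recruitment, unless noted.

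- **Primary test.** The difference in EQ5D change "between SRS and WBRT group will be performed using an independent samples Student"'s t-test, two-sided, alpha 0.05.
- **Other means.** "Means will be compared using independent samples Student"'s t-tests. No alpha is attached to this sentence.
- **Planning inputs.** A "comparison of means with two-sided alpha 0.05 and power of 0.80", for a difference of 0.10 index points "with a standard deviation of 0.25 points". This gives 100 per group, raised to 115 per group for drop-out. One SD and equal arms are used throughout.
- **Repeated secondary endpoints.** These have their own sentence, which assigns them to Kaplan-Meier curves with a log-rank test, or to ANOVA.
- **Survival.** Under Objectives and endpoints, the secondary objective is to "determine whether SRS provides better survival and less toxicity than WBRT".

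The article mentions neither an unequal-variance test nor a variance check. It gives no SD, survival or drop-out figure by arm.

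**The concern.** Student's t-test pools the two sample variances. Pooling does no harm when the arms are of equal size, or when the spreads are equal. When both differ, the pooled standard error is wrong. It is too small if the smaller arm has the larger spread, and too large in the reverse case.

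Randomisation is planned at 115 per arm, but the endpoint is the 3-month score minus the baseline score, so only patients alive and assessed at 3 months contribute. If SRS does improve survival, the scored arms will be unequal. Equal spread is not assured either, since the endpoint is a change on a bounded index, where spread can move with the mean.

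At stake is whether the primary p-value and confidence interval have their stated two-sided 5% property in a setting the trial's own objective makes possible. The direction of any error cannot be known beforehand.

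**Working it through.** **1. The plan's sample size.** From the article: difference 0.10, SD 0.25, two-sided alpha 0.05, power 0.80.

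n per group = 2 × (1.960 + 0.842)² × 0.25² / 0.10² = 2 × 7.85 × 6.25 = 98.1, so 99 by the normal approximation. The t-based solution is 99.08, so 100. Power at 100 per group is 80.4%. Then 100 × 1.15 = 115. The stated figures are reproduced.

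**2. Type I error of the pooled test.** Let the arms have n₁, n₂ scored patients and SDs σ₁, σ₂.

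- Variance the pooled test uses, on average: A = s_p² (1/n₁ + 1/n₂), with s_p² = [(n₁−1)σ₁² + (n₂−1)σ₂²] / (n₁+n₂−2)
- True variance of the difference in means: B = σ₁²/n₁ + σ₂²/n₂
- With R = A/B, type I error ≈ 2[1 − Φ(1.96 √R)]

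If n₁ = n₂, or if σ₁ = σ₂, then R = 1 and the error is 5%. This covers the plan's own inputs.

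**3. One case in full.** Assume 98 v 70 scored, with SD 1 in the larger arm and 1.5 in the smaller (only the ratio matters).

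- s_p² = (97 × 1 + 69 × 2.25)/166 = 252.25/166 = 1.520
- A = 1.520 × (1/98 + 1/70) = 1.520 × 0.02449 = 0.03721
- B = 1/98 + 2.25/70 = 0.04235
- R = 0.879, √R = 0.937, 1.96 × 0.937 = 1.837, error = 6.6%

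**4. Range.** The article supports none of these arm sizes or SD ratios; they are assumptions. Out of 115, 98 scored is a loss of about 15%, 80 about 30% and 70 about 39%.

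| Scored patients | Arm with larger SD | SD ratio | R | Student type I error |
|---|---|---|---|---|
| 98 v 80 | smaller | 1.2 | 0.964 | 5.4% |
| 98 v 80 | smaller | 1.5 | 0.925 | 5.9% |
| 98 v 70 | smaller | 1.2 | 0.941 | 5.7% |
| 98 v 70 | smaller | 1.5 | 0.879 | 6.6% |
| 98 v 80 | larger | 1.5 | 1.081 | 4.2% |
| 98 v 70 | larger | 1.5 | 1.138 | 3.7% |

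Simulation under normality agrees to within about 0.1 point. In the same simulations the Welch test stays between 4.9% and 5.1%. Milder imbalance does less: 110 v 90 with SDs 0.225 and 0.275 gives 5.4%.

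**5. Power cost of Welch.** True difference 0.10, SD 0.25 in both arms, simulated.

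| Scored patients | Student | Welch |
|---|---|---|
| 100 v 100 | 80.4% | 80.4% |
| 100 v 70 | 72.3% | 72.2% |
| 60 v 40 | 49.1% | 48.9% |
| 40 v 20 | 30.1% | 29.7% |

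Where the SDs differ, the two tests reject at different rates because Student's is off its level. At 100 v 70 with SDs 0.20 and 0.30, Student rejects 72.3% and Welch 67.5%, but Student's type I error there is 6.7%. With the SDs swapped, Welch has the higher power (73.7% v 69.0%).

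**The case against.** The strongest objection is that nothing in the article shows a departure from 5%. It plans equal arms and one SD, and with those the pooled test is exact. A departure needs unequal numbers and unequal spread together. A survival objective points at most to unequal numbers, and gives no reason why the smaller arm should be the more variable one. A gap such as 98 v 70 at 3 months is large and is supported by no figure in the article. This stands, and it is why the point is a refinement only.

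Secondly, the equal-variance form is inferred from the name Student. The article does not state it, and a full protocol or analysis plan may specify the unequal-variance version. This also stands. If so, the change only makes the article's wording match.

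Thirdly, a reader might infer that the t-test governs every comparison of means, so that small numbers at 6, 9 and 12 months, or widely spread measures such as steroid dose and the Barthel index, would push the error well beyond the figures above. The article does not support that. Endpoints that repeat in time have their own sentence (log-rank or ANOVA), and the stated 0.05 belongs to the primary comparison and the sample size, not to the sentence on other means. Normal-theory figures would also be a poor guide for steroid dose or Barthel. What remains is narrower: a classical two-group ANOVA at one visit is the same pooled test (F = t²), so the safeguard is worth carrying over to it.

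Finally, if survival differs, the larger problem is that survivors are compared with survivors. Welch does nothing about that selection. This is correct, and is a separate matter.

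**Conclusion.** A low-severity improvement, not an error in the plan. Under the plan's own inputs Student's t-test holds 5%. If the scored arms differ in both size and spread, the primary test's true level moves to between about 3.7% and 6.6% in the scenarios considered, with the sign depending on which arm has the larger SD.

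This rests on assumed arm sizes (70 or 80 v 98), assumed SD ratios (1.2 to 1.5), normality, and the ordinary reading of Student's t-test as the pooled form. It would be going too far to say that the plan misses its stated 5%, or that no trade-off at all is involved. The first is conditional on figures the article does not give, and the second is very nearly but not literally true.

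**What to change.** Under Number of patients and recruitment, and in the analysis plan before any comparison by arm:

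1. Name the Welch (unequal-variance) t-test for the primary EQ5D comparison and for other means compared by t-test.
2. Where the ANOVA sentence applies to repeated endpoints, specify the Welch form, or heteroscedasticity-robust standard errors if a regression model is fitted.

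The choice should be fixed in advance, so that the test is not picked after the variances have been seen.

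Cost: a change of wording. The sample size stays at 230 and no further data are needed. With equal SDs the power loss is nil at 100 per arm, about 0.1 point at 40 v 60 or larger, and up to about 0.5 point at 20 v 40.
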